***A description of the measures taken to minimize/avoid bias, including: (a) Randomization. (b) Blinding.***

In order to minimize/avoid bias, schools will be randomised to the study groups. Balanced randomisation will occur using the online program Research Randomizer. In addition, the Research Officers employed to carry out the baseline and follow-up assessments will be blinded to the group allocations of the schools.

***A description of the trial treatment(s) and the dosage and dosage regimen of the investigational product(s). Also include a description of the dosage form, packaging, and labelling of the investigational product(s)***

*The Climate Schools program:*

The Climate Schools program aims to reduce the use of Australia's most commonly used licit and illicit drugs: alcohol and cannabis, and related harms. The program was pioneered by CI [name], CI [name] and AI [name] and is based on the effective harm-minimisation approach to prevention ([name] et al., 2009a; 2009b; 2009c; McBride et al., 2006; Vogl et al., 2009). The Climate Schools program consists of twelve 40-minute lessons and is designed to fit within the school health curriculum. It is facilitated by the internet which guarantees complete and consistent delivery whilst ensuring high implementation fidelity. It uses cartoon storylines to engage and maintain student interest and involvement over time (Schinke et al., 2004). The first six lessons focus specifically on alcohol and are delivered approximately six months prior to the remaining six lessons which focus on cannabis. The first part of each lesson is completed individually over the internet where students are engaged through cartoon storylines which impart information about the short- and long-term effects of alcohol and cannabis, normative alcohol and cannabis use, refusal skills, and first aid. Students are provided with confidential login details to access the Climate website. The second part of each lesson is a group or class activity delivered by the teacher which reinforces the information in the cartoons and allows interactive communication between students. Teachers are provided with a manual containing the activities, implementation guidelines, links to the education syllabus and summaries for each lesson. (To view the Climate Schools program, visit [www.climateschools.com](http://www.climateschools.com) and logon using the Username: 'Teacher' and Password: 'London').

*The Preventure program:*

The Preventure program is a brief personality-targeted substance use preventive intervention for high-risk adolescents aged 14-15 years. Unlike universal programs, this selected personality-targeted approach addresses four personality risk-factors for early-onset substance misuse and other risky behaviours: Sensation Seeking, Impulsivity, Anxiety Sensitivity and Hoplessness (Woicik et al., 2009). The Preventure program is also consistent with new models which conceptualise substance use as being driven by personality traits such as impulsivity and disinhibition (Dick et al., 2008). This program involves two 90-minute group sessions which are carried out by a trained facilitator and co-facilitator. In the first session, participants are guided in a goal setting exercise, designed to enhance motivation to change behaviour. Psycho-educational strategies are used to teach participants about their target personality variable and associated problematic coping behaviours like avoidance, interpersonal dependence, aggression, risky behaviours and substance misuse. They are then introduced to the cognitive behavioural model and guided in breaking down personal experience according to the physical, cognitive and behavioural components of an emotional response. A novel component to this intervention approach is the fact that all exercises discuss thoughts, emotions and behaviours in a personality-specific way, e.g. identifying situational triggers and cognitive distortions related to Sensation Seeking specifically. In the second session, participants are encouraged to identify and challenge personality-specific cognitive distortions that lead to problematic behaviours. Preventure is the first and only targeted school-based alcohol and illicit drug prevention programme that

has been shown to prevent growth in alcohol and substance misuse in Canada and the UK ([name] et al., 2006; 2008; 2010).

*The CAP Intervention:*

The CAP intervention will combine the Climate Schools and Preventure programs with the aim of providing a comprehensive 'universal' and 'targeted' model to prevent substance use and related harms in Australian adolescents. The CAP study has logos that will be used on all study materials (see Figure 2).

Figure 2. The CAP study logos

[figure not shown]

***The expected duration of subject participation, and a description of the sequence and duration of all trial periods, including follow-up, if any.***

See Table 1 for the intervention and assessment timeline. Participants will be recruited at the start of Year 8 and baselines will be carried out in Term 1. The Climate Schools and Preventure programs will be implemented in Terms 1-3. Follow up assessments will occur during Years 8, 9, 10 and the start of Year 11. Hence participants will in the study for approximately 3 years.

***A description of the "stopping rules" or "discontinuation criteria" for individual subjects, parts of trial and entire trial***

Is it possible that some participants may decide to discontinue with the Preventure program due to emotional distress. Students and will be informed and reminded throughout the study that participation is voluntary they have the option of withdrawing from the study at any time. It will be emphasised that withdrawal from the study will have no effect on their relationship with the school or the University of NSW. If they choose to discontinue they will be referred to the appropriate school staff member/counsellor (with their consent).

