## Assessment of Efficacy

### *Specification of the efficacy parameters*

Treatment efficacy will be determined by analysing changes in three outcome measures over the study period:

1. The uptake and harmful use of alcohol and illicit substances
2. Substance use related harms
3. Mental health comorbidity

This information will be gleaned from the baseline and follow-up assessments using reliable and well-validated measures.

The assessment surveys include the following measures:

1. *Demographic data* including gender, age, academic performance, and truancy rates will be obtained to determine baseline equivalence of the groups
2. *The Substance Use Risk Profile Scale (SURPS)* will be used to assess for variation in personality risk for substance abuse/dependence along 4 dimensions: Sensation Seeking, Impulsivity, Anxiety Sensitivity and Hopelessness. Students who score more than one SD above the school mean on any of the four personality risk subscales will be categorized into these sub-groups and will be invited to participate in the Prevention intervention if they are randomised into the CAP or Preventure groups. If a student has high scores on more than one subscale, they will be assigned to the group in which they showed the most statistical deviance according to z-scores;
3. *Alcohol and cannabis knowledge, Patterns of Alcohol use, Cannabis use and Other substance use, and Attitudes about alcohol* will be assessed using questionnaires adapted from the School Health and Alcohol Harm Reduction Project (SHAHRP; McBride et al., 2003; 2006) and also based on the questions from the National Drug Strategy Household Survey 2007;
4. *Harms caused by cannabis use* will be measured using 12 items from the SHAHRP survey instrument and a set of questions adapted from the Adolescent Cannabis Problems Questionnaire (Martin et al., 2006);
5. Five questions will be used to assess student's *intention to use alcohol and illicit drugs* in the 'future'
6. *The Resistive Self-Regulatory Efficacy Scale* will be used to measure participants' perceived efficacy to resist peer pressure to engage in high risk activities (Bandura et al., 2003);
7. The *Kessler 6 scale* (Kessler et al., 2002) will be used to assess past-month psychological distress
8. The *Strengths and Difficulties Questionnaire* (Goodman, 1998) will be used to assess both positive and negative attributes of the students;

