## Statistics

### ***A description of the statistical methods to be employed, including timing of any planned interim analysis(es)***

Baseline equivalence and attrition between groups will be examined using single-level analyses; one-way analyses of variance to examine normally distributed data, Chi-square to examine binominal data, and Mann-Whitney U-test to examine non-normally distributed data. To examine intervention by time interaction effects, mixed effects regression will be used due to the multi-level and hierarchical nature of the data. To account for intracluster correlations between schools, intervention effects will primarily be examined using hierarchical linear modeling (HLM) for normally distributed data and hierarchical generalized linear modeling using Poisson sampling for count data. Outcome variables will be centered at post-test to allow for comparisons between groups immediately after the intervention and growth terms will be analysed to determine the magnitude of the follow-up effects. Analyses will be conducted using the program HLM 6 (57). If unconditional models reveal that less than 10% of systematic variance exists at the between-school level for any outcome variable, HLM will be abandoned and single-level analyses will be used (58). For these variables, ANCOVAs utilising the SPSS GLM procedure will be conducted to account for any baseline differences that might exist between groups. Bonferroni adjustments will be made for multiple comparisons. Odds ratios and 95% confidence intervals will also be calculated.

Interim analyses will take place at each assessment stage (including the baseline assessment). This will assist with the monitoring of data collection and data entry. Final stage analyses will be carried out at the 36 month follow-up.

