### ***The number of subjects planned to be enrolled***

***In multicentre trials, the numbers of enrolled subjects projected for each trial site should be specified. Reason for choice of sample size, including reflections on (or calculations of) the power of the trial and clinical justification***

To account for cluster randomisation, sample size calculations are based on recent sample size requirements developed by Heo & Leon (2009) to detect intervention by time interactions in longitudinal cluster randomized clinical trials. This trial will be powered to detect differences in the overall sample as well as in the high-risk students also. To allow for comparisons between the high-risk students, 600 high risk students from 20 schools are required (i.e. 30 high-risk students per school and 5 schools per intervention group). This would achieve 80% power to detect a standardized between-group mean difference of 0.3 ( $p = 0.05$ ) in outcomes at the end of the trial with 7 measurement occasions. An effect size of 0.3 is comparable to previous trials of drug prevention programs (Cuijpers, 2002; Tobler & Stratton, 1997). To account for dropouts during the trial which we expect to be approximately 10% ([name] et al., 2009a; [name] et al., 2010), we aim to recruit 80 students per school, 40% ( $n = 32$ ) of whom are expected to be high-risk based on previous research CI [name], and 6 schools per group giving us a total of 1920 students from 24 schools at baseline to test the effect of the intervention in the overall group.

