***The level of significance to be used***

All tests conducted will use a predetermined alpha level of .05.

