## 4. Sample Size (Maximum of 250 Words)

Outline the intended sample size for the project and justify how this will meet the aims of the study.

Sample size calculations tools can be found online at:

- <http://powerandsamplesize.com/Calculators/> (quantitative)
- <http://stat.ubc.ca/~rollin/stats/ssize/index.html> (quantitative)
- [http://eprints.ncrm.ac.uk/2273/4/how\\_many\\_interviews.pdf](http://eprints.ncrm.ac.uk/2273/4/how_many_interviews.pdf) (qualitative)

Participants for this study are 2,190 individuals who were recruited to the original CAP study as students in 2012. Power calculations for the original trial were based on recent methods developed to account for cluster randomisation (Heo et al., 2009). These calculations assumed 20% drop-out, and indicated a total of 1,920 participants recruited from 24 schools would achieve 80% power to detect a between-group mean difference of 0.15 ( $p < 0.05$ ). For comparisons among high risk participants, 600 students from 20 schools would achieve 80% power to detect a standardized between-group mean difference of 0.3. In our original study we achieved well over this recruitment target, with 2,190 students and 947 high-risk students participating in the study.

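### Baseline adjustment is specified for the single-level fallback but not for the HLM post-test contrast, where chance imbalance between six schools per group is largest

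*Protocol*

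**What the plan says.** The Trial Design section allocates schools to four groups, six per group. On method, the section on minimising bias says only that "Balanced randomisation will occur using the online program Research Randomizer", and the section on randomisation codes repeats this. Numbers per group are therefore equal. No stratification, matching or covariate constraint on schools is stated.

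The Statistics section (statistical methods) aims at intervention-by-time effects with mixed models. For the HLM it says "Outcome variables will be centered at post-test to allow for comparisons between groups immediately after the intervention", and the same sentence goes on to use growth terms for the follow-up effects. So two group effects are named: a post-test intercept contrast and a growth contrast. No baseline covariate is named for either.

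If less than 10% of the variance of an outcome lies between schools, HLM is dropped. ANCOVAs are then used, which "will be conducted to account for any baseline differences that might exist between groups". This is the only baseline adjustment the protocol specifies. Under Specification of the efficacy parameters, the demographic items "will be obtained to determine baseline equivalence of the groups".

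The overall-sample target is in the extension's Project Description (4. Sample Size): 1,920 students from 24 schools "would achieve 80% power to detect a between-group mean difference of 0.15". The protocol's own sample-size section gives only the high-risk target of 0.3.

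**The concern.** Equal numbers of schools do not make groups alike. With six schools per group, baseline means will differ by chance, and the size of that difference depends on how much variance lies between schools.

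The 10% rule makes this worse. Outcomes with little between-school variance, where chance imbalance is small, go to a baseline-adjusted ANCOVA. Outcomes with 10% or more, where it is large, stay in an HLM with no stated adjustment. In that HLM the intercept contrast sits at post-test, so a lasting difference that existed before the intervention is read as an immediate effect. At stake is the error of that contrast in the one allocation drawn, and precision that a trial of about two dozen schools can ill spare.

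**Working it through.** **The plan's own figure.** The benchmark is 0.15, read as SD units (the text does not attach the word standardized to it). Ignoring clustering, 480 students per group at two-sided 0.05 give power Φ(0.15 × √(480/2) − 1.96) = Φ(0.364) = 64%. A slope-difference formula with seven occasions gives 2(1−ρ)(1.96+0.84)²/(28 × 0.025²) ≈ 897(1−ρ) students per group. That meets 480 at ρ = 0.47, or 384 (after the 20% dropout the extension states) at ρ = 0.57. No ρ or ICC is given, so the 80% can be neither confirmed nor refuted. The point below uses 0.15 only as a yardstick.

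**Inputs.** Six schools per group and 80 students per school (protocol). HLM only at a between-school share of 10% or more (protocol), read here as ICC ≥ 0.10. Assumed: the baseline ICC equals the outcome ICC.

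**Chance difference between two groups.** SD = √(2[ICC + (1−ICC)/80]/6).

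- At ICC 0.10: ICC + 0.90/80 = 0.11125, so SD = √(2 × 0.11125/6) = 0.193. P(|difference| > 0.15) = 2[1−Φ(0.15/0.193)] = 44%.
- At ICC 0.15: SD 0.231, probability 52%.
- For at least one of the three comparisons with the combined (CAP) group at ICC 0.10: about 78%.
- For comparison, ICC 0.01, 0.02 and 0.05 give SD 0.086, 0.104 and 0.144, and 8%, 15% and 30% per pair. These ICCs fall below the 10% rule, where ANCOVA already adjusts.
- With the numbers recruited (2,190 students, 26 schools, so about 84 per school and 6.5 schools per group) at ICC 0.10: SD = √(2 × (0.10 + 0.90/84.2)/6.5) = 0.185, and the probability is 42%.
- High-risk students (32 per school) against their 0.30 target at ICC 0.10: SD 0.207, and 15% per pair.

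**Pass-through.** Let one group be shifted by a constant δ at every occasion. In a growth model with time zero at post-test, the intercept contrast shifts by δ and the growth contrast by 0. With δ = 0.15, a numerical fit gave 0.15 and 0, whether or not baseline was among the outcome occasions.

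**Gain from adjustment at ICC 0.10.** Assumed correlations over time are 0.5 (student) and 0.7 or 0.8 (school). The correlation of school means is r = (0.10 × ρ_school + 0.01125 × 0.5)/0.11125.

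- ρ_school 0.7: r = 0.680, 1−r² = 0.538.
- ρ_school 0.8: r = 0.770, 1−r² = 0.408.
- Estimating the coefficient from 24 schools in four groups (20 within-group degrees of freedom) multiplies the variance by 1 + 1/(20−2) = 1.056, giving 0.568 and 0.430 of the unadjusted variance: reductions of 43% and 57%, or roughly 45-55%.
- Check with two groups only (12 schools, factor 1 + 1/8): 0.408 × 1.125 = 0.459. A simulation at ρ_school 0.8 gave SE 0.192 unadjusted and 0.130 adjusted, a variance ratio of 0.458.

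**Error rates.** In that simulation with no true effect, a school-level post-test test rejected in about 5.0% of all trials. Among trials with baseline imbalance above 0.15 in either direction it rejected in 10%. Where the imbalance favoured one given group by more than 0.15, the mean spurious post-test difference was 0.201 unadjusted and about 0 adjusted.

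**The case against.** Several stronger readings are tempting, and the documents do not support them.

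- *Randomisation is unrestricted.* It is not: numbers per group are balanced. Only stratification or a covariate constraint is unstated.
- *The HLM as a whole is confounded by baseline.* The stated target is intervention by time, the sample size rests on it, and baseline is one of the seven occasions. A stable difference cancels from the growth contrast; only the post-test intercept contrast is exposed.
- *Imbalance at an ICC of 0.01 to 0.05 shows the fault.* Those outcomes would leave HLM for the adjusted ANCOVA.
- *Equivalence tests decide whether to adjust.* Nothing says so. The switch to ANCOVA depends on the variance share.
- *The result is biased.* Randomisation makes the expected difference zero, and an HLM standard error includes between-school variance.

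It is also fair that silence on HLM covariates is not exclusion, and that a SAP may list them. But the protocol does settle baseline adjustment in one branch and describes the other in some detail without it, so this is more than an omitted covariate list. Finally, the programme is meant to reach students before much substance use occurs. Baseline use may be near floor and predict later use poorly, which would shrink the gain. That stands, and limits the size of the benefit rather than the case for adjusting.

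**Conclusion.** The point holds for the HLM post-test contrast. The specified adjustment goes to outcomes with the smaller chance imbalance; none is stated for those with the larger. At the 10% floor a given pair of groups differs at baseline by more than 0.15 SD in about 44% of allocations, and more often at higher ICC; a stable difference of that kind carries over whole into the post-test contrast. The consequence is lost precision and error in the realised trial. It is not bias on average, and type I error stays near 5% for a test that respects clustering.

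The figures assume planned school numbers and sizes, a baseline ICC equal to that of the outcome, and normally distributed means. The 0.15 benchmark appears only in the extension. The precision gain also rests on the assumed correlations over time. This is a worthwhile improvement to the analysis, not a flaw that invalidates the design.

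**What to change.** In the statistical methods section, state for the HLM post-test contrast one of two approaches:

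1. Model follow-up occasions only, and adjust for the student's baseline value of the outcome and the school-mean baseline.
2. Keep baseline as an outcome occasion, and constrain baseline means to be equal across groups.

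Use one or the other, so that baseline is not both outcome and covariate. Write the same into the models for the 5-, 6- and 7-year surveys; the extension specifies no model for these.

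The cost is wording, through the protocol amendment already foreseen for statistical changes. The baseline surveys already contain the variables. The extension reports that 3-year results exist, so for those the adjusted contrast can only be added and labelled as such.

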***Accountability procedures for the investigational product(s), including the placebo(s) and comparator(s), if any***

N/A

***Maintenance of trial treatment randomization codes and procedures for breaking codes***

Balanced randomization of schools to conditions will be implemented using the online program Research Randomizer (<http://www.randomizer.org/>).

***The identification of any data to be recorded directly on the Case Report Forms (i.e. no prior written or electronic record of data), and to be considered to be source data***

N/A

## **Selection and Withdrawal of Subjects**

### ***Subject inclusion criteria***

Participants are male and female students in Year 8 who are willing to consent to participating in the study. Parental/guardian consent will also be obtained. Participants invited to take part in the Preventure program will be screened as 'high risk' using the Substance Use Risk Profile Scale (SURPS).

### ***Subject exclusion criteria***

There are no exclusion criteria for this study.

### ***Subject withdrawal criteria***

***(i.e. terminating investigational product treatment/trial treatment) and procedures specifying:***

- (a) When and how to withdraw subjects from the trial/ investigational product treatment.***
- (b) The type and timing of the data to be collected for withdrawn subjects.***
- (c) Whether and how subjects are to be replaced.***
- (d) The follow-up for subjects withdrawn from investigational product treatment/trial treatment.***

There are no withdrawal criteria for this study. However, students and will be informed and reminded throughout the study that participation is voluntary they have the option of withdrawing from the study at any time. If a student decides to withdraw, replacements will not be sought.

## Treatment of Subjects

***The treatment(s) to be administered, including the name(s) of all the product(s), the dose(s), the dosing schedule(s), the route/mode(s) of administration, and the treatment period(s), including the follow-up period(s) for subjects for each investigational product treatment/trial treatment group/arm of the trial.***

Table 1 illustrates the intervention and assessment periods for the trial. All participants will be asked to complete the baseline and follow-up surveys. Schools will be randomised to one of four groups; (1) the 'Control' condition (usual classes/assessment only), (2) the 'Climate Schools only' condition, (3) the 'Preventure only' condition, or (4) the 'CAP (Climate Schools and Preventure)' condition.

